# Effect of vaginal antiseptic prior to caesarean section on the rate of post-caesarean complications: a blinded randomised controlled trial

**DOI:** 10.1186/s13063-021-05857-7

**Published:** 2022-03-24

**Keywords:** Caesarean section, Vaginal cleansing, Antiseptic wash, Post-caesarean infection

## Abstract

**Background:**

Rates of caesarean section (CS) delivery are increasing worldwide. CS delivery is often complicated by post-surgical infection, estimated to have ten times higher risk of infections than that of vaginal delivery. While widespread use of prophylactic antibiotics with CS has reduced post-CS infection, incidence may be reduced further by cleansing the vagina with betadine antiseptic wash prior to CS. However, reports are not consistent, and different antiseptics have been practised variably. Therefore, in order to ensure that the risks to the mother are as minimal as possible, it is important to determine whether vaginal irrigation with antiseptic wash reduces post-CS infection rate, and if so, which antiseptic is paramount.

**Methods:**

Women giving birth by elective or emergency CS will be assigned into either the intervention (1% povidone iodine (*n* = 125) or chlorhexidine (*n* = 125)) or the control (no-irrigation (*n* = 125)) group by using a block randomisation technique. Participants will receive vaginal cleansing with an intervention or no vaginal cleansing prior to CS. Follow-up will occur at day 14 and day 28 post-CS. A predeveloped questionnaire will be completed with patients’ socio-demographic characteristics and required clinical and pregnancy-related information. All the fever, infection and readmission-related information will be completed from either the patient’s or their record or at follow-up visits. Occurrence of post-CS infection, as measured by primary and secondary outcomes, will be compared between the groups.

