
### Objectives {7}

#### Hypothesis

H_1_: In a blinded randomised controlled clinical trial, using either chlorhexidine or povidone iodine for vaginal irrigation prior to CS will reduce post-operative infection outcomes by 50% when compared to no vaginal irrigation.

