### Outcomes {12}

#### Primary outcome

The primary outcome is endometritis: defined as tympanic temperature > 38 °C with uterine tenderness and/or foul-smelling vaginal discharge within 28 days of post-CS.

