### Sample size {14}

We assume that the interventions will improve the rate of infection including post-operative infective complications (within 28 days post-CS) by 50% compared to the control. Thus, for sample size estimation in this study, we set *P*_1_ = 8% (as per overall prevalence of post-CS infection range 3–15%), *P*_2_ = 4%, significance level = 5% and the study power = 80%.

Therefore,
$$ n\ge {\left(\frac{Z_{\alpha }+{Z}_{\beta }}{\mathrm{ES}}\right)}^2 $$$$ \mathrm{ES}=\frac{P_1-{P}_2}{\sqrt{P_1\left(1-{P}_1\right)}} $$

*n* ≥ 361

Here, *Z*_*α*_ = 1.96, *Z*_*β*_ = 0.84, *P*_1_ = 0.08, *P*_2_ = 0.04 and *P*_1_ − *P*_2_ = 0.04.

Considering 10% dropout, the study will require recruiting approximately 396 participants for all the groups (*n* = 132 in each group) over a period of 16 months to adequately test the assumption.

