## Statistical methods

### Statistical methods for primary and secondary outcomes {20a}

Baseline characteristics of participants including demographic characteristics, morbidity information with severity, current medication/management and satisfaction towards the current management will be compared using the *t*-test or and *χ*^2^ tests for categorical variables to assess the success of the randomisation. Summary statistics will be presented for all three groups’ infection information. BMI will be calculated using the weight and height of the participants. If required, the analysis will be performed following the ‘intention-to-treat’ analysis method. Primary and secondary outcomes will be compared using ANOVA. Where appropriate, logistic regression analyses will be used to compare the outcomes separately for interventions versus the control group. All data will be entered in MS Excel, and all statistical analyses will be performed using the STATA 11.0 statistical package.

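### The hypothesis is not tied to endometritis, the named primary outcome, so a significant secondary outcome could be claimed as confirming it

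*Protocol article*

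**What the plan says.** The outcomes section is clear. "The primary outcome is endometritis", within 28 days of caesarean section, and three further outcomes are listed as secondary: post-operative fever, wound infection and readmission with infection.

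Other sections use a wider target:

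- **Hypothesis:** either antiseptic "will reduce post-operative infection outcomes by 50% when compared to no vaginal irrigation". The noun is plural and no outcome is singled out.
- **Sample size {14}:** the assumption is that "the interventions will improve the rate of infection including post-operative infective complications (within 28 days post-CS) by 50% compared to the control". The control rate of 8% is taken from an overall range of 3–15% for post-caesarean infection.
- **Abstract, Methods:** "Occurrence of post-CS infection, as measured by primary and secondary outcomes, will be compared between the groups".
- **Plans for assessment and collection of outcomes {18a}:** post-caesarean infection is glossed in brackets as the primary and secondary outcomes.
- **Discussion:** the hypothesis is restated for the general infection rate, and the study conclusions are to come from the primary and secondary outcomes together.
- **Statistical methods {20a}:** "Primary and secondary outcomes will be compared using ANOVA". Logistic regression of each antiseptic against control follows where appropriate.

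The only error level given is in the sample size section: "significance level = 5% and the study power = 80"%, with a critical value of 1.96, hence two-sided.

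**The concern.** Naming one primary outcome protects the error rate only if the confirmatory claim depends on that outcome. Here the claim is worded so that it could be met elsewhere. Suppose endometritis shows no difference and fever is significant at 5%. Under the written hypothesis the authors could report that vaginal antiseptic reduces post-operative infection, and a reader holding the protocol could not say that they had departed from it.

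The objectives look towards a uniform guideline based on the result. It therefore matters whether that guideline would rest on the outcome chosen in advance or on whichever of four crossed the threshold.

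**Working it through.** **1. The plan's own figure.** The stated formula is n ≥ ((Zα + Zβ)/ES)², with ES = (P1 − P2)/√(P1(1 − P1)).

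- ES = 0.04/√(0.08 × 0.92) = 0.1474
- n = (2.80/0.1474)² = 360.6, rounded up to 361
- 120 per group × 1.1 = 132, and 3 × 132 = 396

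The plan's 361 and 396 are reproduced. Both rates entered are overall infection rates. The article gives no rate for endometritis, so the 80% does not refer to the named primary outcome. (Whether this formula suits a comparison between arms is a separate matter, not pursued here.)

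**2. What each section tests.**

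| Section | Target |
|---|---|
| Primary outcome | Endometritis |
| Hypothesis | Infection outcomes, plural |
| Sample size {14} | Overall infection rate |
| Abstract Methods; {18a} | Primary and secondary outcomes together |
| Discussion | General infection rate; conclusions from all outcomes |

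Of these, only the first makes endometritis the target.

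**3. Size of the effect if any one of the four outcomes could confirm the hypothesis.**

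Inputs from the article: four outcomes; three arms at 1:1:1, so the two contrasts with control share a control group and correlate at 0.5; two-sided 5%. Assumed: each test is made at 5%, and the outcomes share a common correlation ρ, which the article does not give. Some positive correlation is expected, because endometritis as defined requires a temperature above 38 °C and so lies within fever.

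With independent outcomes, one antiseptic: 1 − 0.95⁴ = 18.5%. For other values of ρ, I simulated normal test statistics under no effect (400,000 draws). The table gives the chance of at least one false positive.

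| ρ | One antiseptic, 4 outcomes | Both antiseptics, 8 ungated contrasts | Three-group test, 4 outcomes |
|---|---|---|---|
| 0 | 18.6% | 31.7% | 18.6% |
| 0.5 | 15.6% | 26.8% | 15.8% |
| 0.8 | 11.4% | 20.0% | 11.8% |
| 0.9 | 9.3% | 16.5% | 9.6% |

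The last column is an upper limit for both antiseptics if contrasts are read only after a significant three-group test.

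A separate simulation with binary outcomes, 120 per arm, endometritis nested in fever and assumed event rates gave 15.0–15.7% per antiseptic and 26.0–27.0% over both. This agrees with the row for ρ = 0.5.

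**4. The comparator.** With endometritis alone decisive, the rate is 5% per antiseptic. Over two ungated contrasts with a shared control it is 9.1%, and behind a three-group test it is at most 5%. So part of the 16–32% for both antiseptics comes from having two active arms, not from having four outcomes.

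**The case against.** The strongest reply is that no section says one significant outcome is enough. The hypothesis can be read as one overall infection rate, which is how the sample size and Discussion phrase it; that would be a single test with no inflation across outcomes. It can also be read as requiring every outcome to fall, which would be conservative. The outcomes are ranked by label in the usual way. The 5% level is stated for the sample size and not for each test. Using one method for primary and secondary outcomes is ordinary practice, and a testing order or alpha split may sit in an analysis plan that is not shown.

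Much of this stands. A reader might infer that all four outcomes are to be tested at 5% with no hierarchy, giving a false-positive rate of 16% per antiseptic and 27% overall. The article does not support that as a statement of fact. It ranks the outcomes by label and gives no rule that any outcome suffices. The 16% and 27% depend on an assumed correlation of 0.5. The 27% also needs eight ungated contrasts, whereas the methods put a three-group comparison first and the separate regressions only where appropriate, and it includes the two-arm component.

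The reply does not remove the conflict. If one overall infection rate is the target, it is not the named primary outcome. If all outcomes must fall, the article nowhere says so. The absence of a multiplicity method is not the point. The hypothesis belongs to the protocol, and its present wording disagrees with the primary outcome section whatever an analysis plan adds.

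**Conclusion.** The point holds as an inconsistency between the named primary outcome and the hypothesis, with a conditional consequence for error control. If any of the four outcomes could confirm the hypothesis at two-sided 5%, the false-positive chance per antiseptic is about 9–19% for an assumed correlation of 0.9 to 0, against 5% for endometritis alone. Over both antiseptics it is about 16–32% ungated, against about 9% for endometritis alone, or at most about 10–19% behind the three-group test. At the high-correlation end the excess is modest, a little under twice 5%. The stated power of 80% is for overall infection and cannot be carried over to endometritis. The point deserves correction because it governs what the trial may conclude.

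**What to change.** - **Hypothesis, and its restatement in the Discussion:** reword so that it is tested on endometritis within 28 days.
- **Abstract Methods, {18a} and {20a}:** state that fever, wound infection and readmission with infection are secondary and supportive, reported as effect estimates with 95% confidence intervals, and cannot establish the hypothesis on their own. If confirmatory secondary claims are wanted, test these outcomes in a fixed, stated order, and only after endometritis is significant.
- **Sample size {14}:** say that 8% versus 4% is an overall infection rate and that the 80% power does not apply to endometritis.

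The change should be dated and made before outcomes are compared by arm. It needs no extra patients or data. It has two costs: a positive secondary outcome alone can no longer be reported as confirming the hypothesis, and the power statement must be qualified. It does not address the two-arm component (about 9% over two ungated contrasts on endometritis), which needs its own rule.

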**Discussion:**

The results of this study may provide important data to define the future uniform use of vaginal antiseptic wash immediately prior to CS and to determine the best antiseptic wash details in reducing post-operative infections or complications.

**Trial registration:**

Australian New Zealand Clinical Trials Registry (ANZCTR) ACTRN12620000971932p. Registered on 28 September 2020

## Administrative information

Note: the numbers in curly brackets in this protocol refer to SPIRIT checklist item numbers. The order of the items has been modified to group similar items (see http://www.equator-network.org/reporting-guidelines/spirit-2013-statement-defining-standard-protocol-items-for-clinical-trials/).

## Introduction

### Background and rationale {6a}

Caesarean section (CS) is one of the methods of operative delivery in childbirth, and its rate has increased internationally over the last 3 decades for various reasons. According to the Australian Institute of Health and Welfare, the CS rate in Australia was 34% in 2016 [1]. Similar to any other surgical procedure, CS has morbidity in the form of infections, which include endometritis in addition to surgical site infection (SSI). This is a matter of concern as it has been reported that CS can have ten times higher risk of infections than that of vaginal delivery [2]. Furthermore, higher rates of infection have been identified in women with ruptured membranes and in women who undergo a CS in labour [3]. Such infections cause additional burden not only to the mother herself, but also to the newborn and her family as a whole. It also increases the risk of hospital readmissions and cost to health care systems across the world [4]. Olsen et al. demonstrated that wound infection and endometritis may incur an additional cost of US $4200 and US $4500 to the health systems, respectively [5]. Evidence favours the use of prophylactic antibiotics for CS to reduce post-operative infections by 60–70%, as well as the cost and duration of hospitalisation [6–8]. However, there are debates regarding single versus multiple doses, routes and timing of antibiotic use, type of antibiotics and duration. To reduce the rate of post-CS infections further, different antiseptics have been practised inconsistently for skin preparation and vaginal toileting. It has been demonstrated that vaginal preparation with povidone iodine or chlorhexidine solution compared to saline or not cleansing immediately before CS probably reduces the risk of post-CS infection [3]. However, a Cochrane review suggests no clear evidence favouring the use of chlorhexidine solution before surgery over other washing products to prevent SSI [9], while another Cochrane review reported that use of either chlorhexidine or povidone iodine before CS did not make any or might make little difference to the SSI or endometritis [2]. On the other hand, the World Health Organization (WHO) recommends the use of povidone iodine for vaginal cleansing immediately before CS to reduce maternal infection morbidities [10]. This recommendation is further emphasised in a recent systematic review and network meta-analysis by Roeckner et al. which reported that the use of 1% povidone iodine for pre-surgical vaginal irrigation among women who underwent CS had the most beneficial outcomes in the reduction of fever, wound infections and endometritis [11]. Despite the above measures, SSI incidence ranges from 3 to 15% [12], perhaps due to the variability of practices and individual preferences to one antiseptic agent over the other. Given the current limited data, it is imperative to identify the best evidence-based practice for uniform use of antiseptic agents for vaginal toileting to reduce post-CS infections or complications and to standardise their practice in a regional Australian hospital for enhanced recovery after caesarean delivery (ERAs).

### Objectives {7}

#### Hypothesis

H_1_: In a blinded randomised controlled clinical trial, using either chlorhexidine or povidone iodine for vaginal irrigation prior to CS will reduce post-operative infection outcomes by 50% when compared to no vaginal irrigation.

#### Aims

The aims are to introduce uniform use of vaginal antiseptic wash immediately prior to CS and to determine the best antiseptic wash material in reducing post-operative infections or complications.

#### Objectives

The following are the objectives:
To determine the number of post-CS infections among women that will undergo pre-operative vaginal cleansing with either 1% povidone iodine or chlorhexidine or no toileting (control) during elective CSTo determine the number of post-CS infections among women that will undergo pre-operative vaginal cleansing with 1% povidone iodine or chlorhexidine or no toileting (control) during emergency CSTo compare the rate of infections among the three groups that receive either 1% povidone iodine or chlorhexidine or no toileting for vaginal irrigation prior to any kind of CSTo identify the best antiseptic wash and methods for vaginal irrigation prior to CS for developing a uniform guideline through locally generated evidenceTo determine the factors that may influence the outcomes, such as post-CS infections or related complications

### Trial design {8}

This will be a single-centre, three-arm, single-blind, randomised controlled trial. A total of 396 eligible patients will be randomised in a 1:1:1 ratio to receive pre-operative vaginal cleansing with 1% povidone iodine or chlorhexidine or no toileting (control) immediately prior to CS.

## Methods: participants, interventions and outcomes

### Study setting {9}

The study will be conducted in the Obstetrics and Gynaecology Department of Goulburn Valley Health, a regional Australian public hospital.

### Eligibility criteria {10}

#### Inclusion criteria

The inclusion criteria are any patients undergoing either emergency or elective CS that provide voluntary informed consent.

#### Exclusion criteria

The following are the exclusion criteria:
Patients having signs of chorioamnionitis, intrapartum pyrexia and other signs of infection will be excluded from the study.Patients who develop intrapartum pyrexia as a result of syntocinon drip, prolonged labour or obstructed labour and provided voluntary informed consent will be included in the study initially. Their placental swabs will be taken for microscopic examination, culture and sensitivity (mcs). They will be excluded from the study only if their swab results are positive for mcs.Face presentation.Vaginal delivery.Patients who have known allergies to iodine or chlorhexidine.

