#### Assessment of infection

A third person with adequate clinical acumen independent to the project will assess the post-CS infection to reduce any potential bias, for example, the obstetrics and gynaecology consultant on call and obstetrics and gynaecology registrar.

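### The post-operative fever outcome has no rule for fever already present at caesarean section, although the eligibility rules keep some women who were febrile in labour

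*Protocol article*

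**What the plan says.** **Eligibility.** The protocol article, under Exclusion criteria, opens with a general bar: "Patients having signs of chorioamnionitis, intrapartum pyrexia and other signs of infection will be excluded from the study". The next item makes an exception: "Patients who develop intrapartum pyrexia as a result of syntocinon drip, prolonged labour or obstructed labour and provided voluntary informed consent will be included". Placental swabs are then taken, and "They will be excluded from the study only if their swab results are positive for mcs". The section on discontinuing or modifying allocated interventions {11b} repeats that it is the febrile, swab-positive women who may be withdrawn.

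**Outcomes.** Post-operative fever, a secondary outcome, is a tympanic temperature above 38 °C, counted whenever it occurs up to day 28 after CS. The definition asks for no second reading and does not mention fever present before surgery. Endometritis, the primary outcome, needs the same temperature "with uterine tenderness and/or foul-smelling vaginal discharge within 28 days of post-CS".

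**Assessment and analysis.** Under Assessment of infection, "A third person with adequate clinical acumen independent to the project will assess the post-CS infection to reduce any potential bias". The section on additional analyses {20b} says that none are planned.

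**The concern.** Two stated rules do not fit together. One keeps in the trial women who were febrile in labour, provided the swab is negative. The other scores fever on temperature alone and does not separate new fever from fever carried into theatre. Vaginal cleansing is given immediately before CS and cannot prevent a fever that has already begun. If that fever is still above 38 °C afterwards, it becomes an outcome event whichever arm the woman is in.

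Randomisation spreads such events evenly in expectation, so they do not favour an arm. They add the same background to each arm and move the risk ratio towards 1. The trial's hypothesis is relative (a 50% reduction), so this is the scale on which the fever result will be read.

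**Working it through.** **1. Who stays in and what is scored.**

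| Situation | Retained? | Post-operative fever | Endometritis |
|---|---|---|---|
| Labour fever from a listed cause, swab positive | No | – | – |
| Same, swab negative, settled before CS | Yes | Not on the natural reading, since the outcome is post-operative | No |
| Same, swab negative, still above 38 °C after CS | Yes | Yes, in any arm | Temperature component only |

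The third row is the problem.

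**2. Inputs.** From Sample size {14}: control rate P1 = 8% ("as per overall prevalence of post-CS infection range 3–15"%), a reduction "by 50% compared to the control" so that P2 = 4%, and "significance level = 5% and the study power = 80"%. The protocol sets these rates for infection including infective complications. Using them for fever is an assumption. The share of women whose entry fever is scored, g, is not in the document. It is assumed here to be 2%, 5% or 10%.

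**3. The plan's own figure.** ES = 0.04/√(0.08 × 0.92) = 0.1474, and n = (2.80/0.1474)² = 360.64, rounded up to 361. The stated figure reproduces. It serves here only to fix the planning rates and a group size of about 361/3 = 120.

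**4. Dilution of the fever outcome.** If a share g in every arm is an event whatever the treatment:

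- observed rate = g + (1 − g)P
- risk ratio = [g + (1 − g)P2] / [g + (1 − g)P1]
- risk difference = (1 − g)(P1 − P2)

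For g = 5%: control 0.05 + 0.95 × 0.08 = 12.6%; antiseptic 0.05 + 0.95 × 0.04 = 8.8%; ratio 0.088/0.126 = 0.70; difference 0.95 × 4.0 = 3.8 points.

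| g (assumed) | Control | Antiseptic | Risk ratio | Risk difference (points) | Power, 120 per arm |
|---|---|---|---|---|---|
| 0 | 8.0% | 4.0% | 0.50 | 4.0 | 25.5% |
| 2% | 9.8% | 5.9% | 0.60 | 3.9 | 20.2% |
| 5% | 12.6% | 8.8% | 0.70 | 3.8 | 15.6% |
| 10% | 17.2% | 13.6% | 0.79 | 3.6 | 11.7% |

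Power is for a two-sided 5% comparison of two proportions a and b with m = 120 per arm and p̄ = (a + b)/2: Φ{[(a − b) − 1.96√(2p̄(1 − p̄)/m)] / √[(a(1 − a) + b(1 − b))/m]}.

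**5. If not every entry fever persists.** With 5% febrile at entry and half of them scored, g = 2.5%: rates 10.3% v 6.4%, risk ratio 0.62. With a quarter scored, g = 1.25%: risk ratio 0.57. The table is therefore an upper bound for each febrile share.

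**6. Endometritis.** None of these figures applies to it. Tenderness or foul-smelling discharge is also required, and the document gives no basis for saying how often either would accompany a carried-over fever.

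**The case against.** - **The primary outcome is largely protected.** A reader might infer that a woman febrile at entry is already an endometritis case, or nearly one because a fresh uterine incision is tender. The definition does not support the first, and no passage supports the second. This stands and limits the point.
- **The window has a start.** A reader might also infer that any temperature in labour counts. The outcome is named post-operative and its window is expressed relative to CS, so counting naturally begins at CS. This stands too: what is missing is a rule for fever carried over, not a starting point.
- **The affected group is narrow.** Only fever put down to three causes is admitted, swab-positive women are removed, and elective cases are enrolled as well. This is fair, and it is why the size cannot be fixed.
- **An independent clinician judges infection.** That makes mechanical scoring of every reading less certain. But the assessor works to the written definition, which does not tell them to set carried-over fever aside.
- **The harm is modest.** The risk difference hardly moves, no arm is favoured in expectation, and power at 120 per arm is only 25.5% before any dilution, so this is not the main obstacle to detecting an effect. All of that stands. A chance imbalance in febrile entrants is possible, but the same is true of any baseline risk factor.
- **The article is condensed.** Measurement timing may sit in the full protocol. The point, however, concerns two rules that the article does state and that conflict in their effect.

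**Conclusion.** The point holds for post-operative fever, a secondary outcome. As written, a labour fever in a swab-negative woman that persists after CS is an event in any arm, and the relative effect on fever is biased towards the null. For endometritis the exposure is limited to the temperature component, and no size can be given.

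The upper bound for fever is a risk ratio of 0.60, 0.70 or 0.79 in place of 0.50 at febrile shares of 2%, 5% or 10%. It rests on three assumptions: the shares themselves, new-event rates of 8% v 4% borrowed from the sample size section, and every entry fever being scored. The document does not support the stronger conclusion that this could by itself mask the effect on the primary outcome. It is a real but contained defect that is cheap to repair.

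**What to change.** 1. Reconcile the two pyrexia statements under Exclusion criteria with each other and with the outcome definitions, so that it is clear which women febrile in labour are in the analysis.
2. In the primary and secondary outcome definitions, state that the temperature criterion counts new-onset fever after CS. For a woman febrile before CS, a later reading above 38 °C would count only after a recorded temperature of 38 °C or below.
3. Take the pre-CS temperature of every woman from the routine chart. The list of items in section {18a} is illustrative, so this may already be collected.
4. Amend section {20b} to add a sensitivity analysis of the fever and endometritis comparisons without women febrile at entry.

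The cost is some wording, one field from existing records and one repeated analysis. The small downside is that a true infection in a woman whose fever never settles would not count in the main definition. A fixed 24-hour lag for all women is optional and not needed; it would also discard genuine early events.
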